## **4. Statistical Analysis Plan**

### **4.1 Sample size calculation**

In a previous study of patients recovering from coronary artery bypass graft surgery, the incidence of postoperative delirium was 35%.[47] We powered our trial to detect a 50% relative reduction in delirium from a 35% baseline consequent to cognitive training. 96 patients were required in each group for a two-tailed  $\alpha=0.05$  with 80% power. Assuming a potential dropout rate of 10%, we included a total of 214 patients (107 in each group).

## 4.2 Statistical methods

### 4.2.1 Data set

Modified intention-to-treat analysis (m ITT) was defined that patients were primarily analyzed within the groups to which they were assigned, whether or not the minimum compliance threshold of training was met, excluding those without any record of follow-up or cancelled surgeries. Primary indicators are analyzed according to the m ITT principle.

Per protocol set (PPS) refers to the set of cases that meet the minimum compliance threshold of training, have completed the treatment protocol. The PPS is a subset of the ITT in which each subject in the dataset is a valid case or sample with good adherence, no protocol violations, and complete baseline values for key indicators.

### 4.2.2 Data presentation

Quantitative data: Kolmogorov-Smirnov test was used to estimate the distribution of continuous variables. Data will be presented using mean  $\pm$  standard deviation or median (upper and lower quartiles, IQR) according to the normality of data.

Categorical data: Data will be presented using frequencies, composition ratios, or percentages.

### 4.2.3 General considerations

**Data set:** The assessment of primary endpoint will be performed based on m ITT set. The per protocol set is mainly used for sensitivity analysis. Patients who engaged in cognitive training for 3 or more hours were considered to have met our minimum compliance threshold, and included in per protocol set. The establishment of this threshold is derived from the results of our preliminary meta-analysis.

**Covariates and subgroup analysis:** Subgroup analysis will be performed and the subgroup analysis will be carried out as exploratory. To evaluate treatment effect heterogeneity on the primary outcome, predefined subgroup analyses were performed based on surgical methods, age, sex, education level, and baseline cognitive function. Interactions between cognitive training and each variable were assessed by adding interaction terms to the logistic regression model.

**multi-center effect analysis:** This is a multicenter RCT study, and there may be center effects among different centers. The logistic regression models will be used to control the multi-center effect, with the different centers set as fixed effect.

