Just recently, cognitive reserve is regarded as a potentially modifiable protective factor that may guard against the development of postoperative delirium and postoperative cognitive dysfunction.[35] Despite strong evidence favoring the ability of cognitive activity (structured and unstructured) to enhance cognitive reserve, our preliminary systematic review and meta-analysis revealed a notable scarcity of studies applying cognitive activity to perioperative patients to counteract postoperative cognitive impairment, particularly in the context of cardiac surgery with postoperative delirium as the primary outcome.[36] Our meta-analysis included only a few randomized controlled trials on perioperative cognitive training, most of which were small-sample feasibility studies. The Prevention of Early Postoperative Decline trial,[37] a feasibility study of 40 patients having cardiac surgery, suggested that patients scheduled for elective cardiac surgery were more likely comply with cognitive training in the preoperative stage, compared to other stages of the perioperative period. Another in-hospital cognitive training trial with consistent supervision, along with allotted breaks to prevent stress and help consolidate learning, provided some meaningful gains in cognitive function.[38] However, this study is also merely a pilot investigation that conducted postoperative cognitive training on a cohort of 50 patients. And finally, a recent randomized trial reported that preoperative cognitive training reduced delirium by 42% in older patients recovering from major noncardiac surgery, which, however, was derived from a post hoc analysis that removed 4 patients who did not meet the minimum adherence criteria.[39] Hence, there is currently still a lack of strong evidence to demonstrate whether cognitive training can be applied to surgical patients and whether it truly can, by enhancing the preoperative cognitive reserve of patients, to some extent, counteract the adverse cognitive effects of surgery and anesthesia, ultimately reducing the risk of postoperative cognitive impairment.

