Patients were instructed to spend 10 hours on cognitive training. We asked patients to spend at least a full hour per day, over two or three sessions, and that daily sessions include at least one game from each of the six available cognitive domains, more as time permits. A minimum of 10 days of training prior to surgery is needed, equaling a preoperative exercise dose of at least 10 hours. The patients were systematically guided to complete cognitive games in each domain successively. After finishing a game in one cognitive domain, they immediately moved to the next one, and this sequential training ensured that each patient underwent comprehensive exercises in 6 cognitive domains. Participants were free to choose the timing of each training session. The Light of Future software will ensure that each patient is exposed to the same set of games.

Considering that each game includes a tutorial of several tens of seconds, and patients may potentially linger in a game due to various reasons without actively participating but still being automatically timed. Hence, it is necessary to distinguish between the actual in-game time and time spent outside of the game. Because each game is limited by a countdown timer, with each game lasting approximately 58 seconds. We consider the time spent lingering in a game for over two minutes with a completion rate of less than 50%, and those abruptly quitting before reaching 50% completion as invalid training time. If a patient exits a game midway after exceeding 50% completion, the actual effective training duration is calculated based on the completion percentage generated within that game. Additionally, when calculating the actual in-game participation time, we exclude the tutorial time at the beginning of each game.

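### The per-protocol set rests on a training-hours threshold that routine-care patients cannot meet, so the named sensitivity analysis is undefined for one arm or filters only the other after randomisation

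*Protocol*

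**What the plan says.** Section 4.2.1 defines the set without naming an arm: "Per protocol set (PPS) refers to the set of cases that meet the minimum compliance threshold of training, have completed the treatment protocol". It adds that each member must be a "valid case or sample with good adherence, no protocol violations, and complete baseline values for key indicators". Section 4.2.3 supplies the cut-off, "Patients who engaged in cognitive training for 3 or more hours were considered to have met our minimum compliance threshold", and its source: "The establishment of this threshold is derived from the results of our preliminary meta-analysis". The same section uses the PPS mainly for sensitivity analysis. The primary endpoint is analysed in the mITT set, whatever the hours trained.

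Section 3.3.3 gives the routine-care group no cognitive training. Section 3.3.2 instructs the training group to complete 10 hours and states: "A minimum of 10 days of training prior to surgery is needed, equaling a preoperative exercise dose of at least 10 hours".

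**The concern.** A per-protocol rule has to say who qualifies in each arm. This one is written in hours of training, which one arm cannot accrue, so as worded it yields no comparison.

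The obvious repair is to exempt controls from the threshold. That keeps in the training arm only patients who went on to train enough, with no matching removal from routine care. Any prognostic difference between patients who train and patients who do not then enters the treatment comparison.

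At stake is how the primary result is read. A PPS result more favourable than the mITT result could be taken as confirmation of it, or as rescue of a null one, when selection alone could produce it.

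**Working it through.** **The plan's own figure.** Section 4.1 gives 35% against 17.5% (a 50% relative reduction), two-sided alpha 0.05 and 80% power. With unpooled variance, n = (1.96 + 0.8416)² × (0.35×0.65 + 0.175×0.825) / 0.175² = 95.3, so 96 per group. For 10% dropout, 96/0.9 = 106.7, so 107 per group and 214 in total. Both stated figures reproduce, and the point does not rest on them.

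**Who can enter the PPS.**

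| | Training arm | Routine care |
|---|---|---|
| Training available (3.3.2, 3.3.3) | 10 hours instructed | none |
| Can reach 3 hours (4.2.3)? | yes | no, 0 hours by design |
| Other conditions (4.2.1) | apply | apply |
| PPS, literal reading | those with at least 3 hours | nobody |
| PPS, controls exempt from threshold | those with at least 3 hours | those meeting the other conditions |

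**Size of selection under no effect.** Let both randomised arms have 35% risk (the section 4.1 control rate). Let a fraction f of trainees fall below 3 hours, with risk r. The protocol gives neither f nor r, so both are assumptions. The risk among remaining trainees is (0.35 − f·r)/(1 − f), and the apparent risk ratio is that figure divided by 0.35.

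| f | r | Remaining trainees | Apparent RR |
|---|---|---|---|
| 10% | 45% | 0.305/0.9 = 33.9% | 0.97 |
| 10% | 55% | 0.295/0.9 = 32.8% | 0.94 |
| 30% | 45% | 0.215/0.7 = 30.7% | 0.88 |
| 30% | 55% | 0.185/0.7 = 26.4% | 0.76 |

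**Effect on the false-positive rate.** A second parameterisation sets the risk of low-hour trainees at k times that of the rest, with 96 randomised per arm and, as a simplification, every control kept. The remaining trainees' risk is 0.35/((1 − f) + f·k). Rejection rates use the normal approximation to the two-sided test at 0.05.

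| f | k | Apparent OR | Rejection rate |
|---|---|---|---|
| 5% | 1.25 | 0.98 | 5.0% |
| 10% | 1.5 | 0.93 | 5.6% |
| 20% | 1.5 | 0.87 | 7.2% |
| 20% | 2 | 0.77 | 12.7% |
| 30% | 2 | 0.68 | 18.9% |

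**A randomisation-based alternative.** Controls have no access to training, so non-compliance is one-sided. The complier average causal effect (CACE) is the mITT risk difference divided by π, the proportion of the training arm reaching the threshold. A zero risk difference stays zero. At the planned difference of 0.175 it gives 0.175/0.9 = 0.194 for π = 90% and 0.175/0.7 = 0.25 for π = 70%.

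If training below 3 hours also lowers risk, by an amount d among those patients, the 3-hour version overstates the effect in compliers by d(1 − π)/π.

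**The 3-to-10-hour patient.** Section 4.2.3 admits this patient to the PPS. Section 4.2.1 requires a completed treatment protocol and no violations. Section 3.3.2 says at least 10 hours is needed. Read together, the last two arguably exclude the same patient.

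**The case against.** A threshold of training is naturally understood to apply to those assigned to train, and a control-arm rule is the kind of detail a SAP may hold. That is fair as to intent. But the protocol does state the rule, states it without an arm, and the workable reading is the one that filters a single arm. Clarifying the wording does not remove the selection.

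A reader might go further than the text allows in four ways.

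- **That 3 hours contradicts 10 hours.** A compliance cut-off below the instructed dose is ordinary, and this one has a stated source. The protocol foresees shortfall: its recording example in section 3.3.2 is a patient with 6 to 7 hours, the mITT definition covers patients below the threshold, and aim (4) in section 2.2 studies dose-response. Only the membership ambiguity for 3 to under 10 hours stands.
- **That trainees are compared with all controls.** The document does not say so. The conditions on violations and baseline data name no arm and could remove controls too.
- **That the analysis is certainly biased towards benefit.** Section 3.3.2 makes this plausible: training starts only after basic proficiency, and poorly completed games do not count as training time. But no passage shows that low-hour patients are at higher risk. The same section describes first-day correction and daily device collection, which may keep non-compliance low, and at 5 to 10% non-compliance the distortion is small.
- **That the Background condemns this same step.** It notes that an earlier trial's result "was derived from a post hoc analysis that removed 4 patients who did not meet the minimum adherence criteria". The main fault named there is that the analysis was post hoc. Here the exclusion is prespecified and confined to a supporting analysis. What the two share is the removal of non-adherers, and prespecification does not cure that.

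The objection to replacing the PPS outright with a CACE also stands. One or two hours of training may have some effect. That would break the exclusion restriction and overstate benefit, and a CACE rescales the mITT estimate rather than checking it independently.

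**Conclusion.** The point holds for the sensitivity analysis. As written, the PPS has no controls. As it would have to be applied, its hours filter acts on the training arm alone, after randomisation, so the comparison is observational in character.

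The direction depends on low-hour patients being at higher risk, which is plausible but not documented. The size depends on the assumed f and r: an apparent RR of about 0.97 to 0.76 with no true effect. False-positive rates in the second set of scenarios run from 5.0% to 18.9%, and rates above 10% appear only with 20 to 30% non-compliance and doubled risk.

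The primary mITT analysis and the sample size stand. The PPS status of patients with 3 to under 10 hours is a separate ambiguity of wording. Nothing here judges which number of hours is right.

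**What to change.** 1. In section 4.2.1, state that the training threshold applies to the training arm only and that every other PPS condition applies equally to both arms.
2. In section 4.2.3, label the PPS comparison supportive and non-randomised, and say that it neither confirms nor rescues the mITT result.
3. Add a CACE with randomisation as the instrument: the mITT risk difference divided by the proportion of the training arm reaching the threshold, with a confidence interval. Repeat it with compliance defined as any training. Take that second definition from the application's usage log, because section 3.3.2 rounds total hours down and would record less than one hour as zero.
4. Reconcile sections 3.3.2, 4.2.1 and 4.2.3 so that a patient with 3 to under 10 hours is clearly in or out of the PPS.

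The cost is a few sentences and one additional analysis on data already collected. The downsides to name are a wider confidence interval and the 3-hour version's assumption that training below 3 hours has no effect, since it overstates benefit if that fails. The any-training version avoids that assumption but estimates the effect in a broader group of trainees.

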#### **General analysis:**

The data analyses mainly include statistical description and statistical inference. Quantitative data will be described by central tendency and dispersion tendency. The normally distributed data of central tendency and dispersion tendency will be described as means and standard division, respectively. The non-normally distributed data of central tendency and dispersion tendency will be described as median and quartiles. The qualitative data will be described as frequency and percentage. Statistical inference,

independent t test or non-parameter test will be used to compare the quantitative data between the two groups, while chi-square test or Fisher's exact test will be used for comparing the qualitative data between the two groups.

For missing data, imputation techniques were used. Statistical analyses were performed using SPSS 23.0 (IBM SPSS) and R (R software 4.2.1), and 2-sided  $P < 0.05$  was considered to be statistically significant in all statistical tests.

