### **3.7. Outcome measures**

#### **3.7.1 Preoperative measures**

(1) Demographic information: age, sex, height, weight, body mass index, education level, cognition;

- (2) Medical history: past history, history of anesthesia, ASA classification, comorbidities, diagnoses;
- (3) Procedure: type of procedure;
- (4) Circulatory indicators: pre-anesthesia vital signs (heart rate, [HR], systolic BP [SBP], diastolic BP [DBP], SpO2, respiratory rate [RR]);
- (5) Laboratory examination: Blood routine examination, liver and kidney function;
- (6) Mental state: used by Geriatric depression scale;
- (7) Preoperative cognitive function status: used by Montreal Cognitive Assessment (MoCA); [41]
- (8) Presence of delirium before surgery: used by Confusion Assessment Method (CAM);[42]
- (9) Preoperative frailty: used by the Frail Scale.

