**Secondary outcomes:**

- (1) cumulative incidence of POD
- (2) incidence of severe delirium, evaluated with the Memorial Delirium Assessment Scale (MDAS)[46]
- (3) postoperative cognitive dysfunction (POCD) on postoperative day 7 or at discharge if earlier, used by the Montreal Cognitive Assessment (MoCA) (range, 0 [worst] to 30 [best]), defined as a 1 standard deviation decrease from baseline in Montreal cognitive assessment score at postoperative day 7 or discharge.
- (4) cognitive function one month after surgery, used by the Revised Telephone Interview for Cognitive Status (TICS-m) (range, 0 [worst] to 50 [best])
- (5) 30-day all-cause mortality
- (6) durations of intensive care unit (number of days in the intensive care unit from the end of operation to discharge) and postoperative hospital care.
- (7) elapsed time from the end of surgery to delirium onset
- (8) duration of delirium (defined as the period between the first and last delirium-positive day, even if there were non-delirious days in between)
- (9) the total number of delirium-positive days in patients who developed delirium
- (10) cognitive function at three time points (baseline, preoperative, postoperative day 7 or at discharge if earlier. was used to assess early POCD on the seventh day after surgery or at discharge and cognitive function at any time points before or after surgery.
- (11) Postoperative intubation time, defined as duration from the end of the procedure to extubation.
- (12) intensive care unit readmission within 30 days after surgery.
- (13) Number of days alive and out of the hospital within 30 days. (The sum of the number of days patients were alive and not in the hospital within 30 days after surgery. It is calculated as 30 days minus the total number of days in hospital after surgery (maximum 30 days, minimum 0 days). If the patient is not hospitalized from 00:00 to 24:00 in a day, the number of days without hospitalization can be counted; After discharge, patients were hospitalized for a second time, and the second hospitalization time was also included in the total number of days in hospital. The patient died within 30 days of surgery. DAOH 30 is 0 days; If the patient was not discharged 30 days after surgery, DAOH 30 was recorded as 0 days.)

All outcomes were assessed by investigators masked to patient allocation.

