#### **4.2.5 Analysis of other endpoints**

For secondary and exploratory endpoints, continuous data will be presented as means (SDs) or median (IQRs), as appropriate. The secondary endpoint followed no Gaussian distribution, will be presented as median (interquartile range) and tested by Mann-Whitney U test. POCD was defined as a 1 standard deviation decline in MoCA score on postoperative day 7, or at discharge if earlier, compared to baseline. This definition aligns with previous definitions of POCD and current recommendations for defining POCD or delayed neurocognitive recovery. [48,49] Mantel-Haenszel  $\chi^2$  and Cuzick tests assessed a potential dose-response relationship between the total hours of cognitive training and incidence of delirium. Analyses of delirium duration and delirium-positive days were conducted using the Zero-inflated Poisson regression model. Regarding the assessment of delirium severity, ordinal logistic regression model was used to model no delirium, delirium and severe delirium. Additionally, a post-hoc analysis incorporating study site, age, surgical technique, baseline educational level and cognitive function of the participants was conducted.

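### Preoperative MoCA, day-7 MoCA and one-month TICS-m are assigned unadjusted two-group tests although baseline MoCA is collected; the tests are valid but give up precision

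*Protocol*

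**What the plan says.** The default tests are in protocol section 4.2.3, under General analysis. For continuous outcomes, "independent t test or non-parameter test will be used to compare the quantitative data between the two groups". For categorical outcomes, "chi-square test or Fisher's exact test will be used for comparing the qualitative data between the two groups". Section 4.2.5 says that non-Gaussian secondary endpoints "will be presented as median (interquartile range) and tested by Mann-Whitney U test".

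The cognitive outcomes are in section 3.7.3:

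- Secondary outcome 10 is "cognitive function at three time points (baseline, preoperative, postoperative day 7 or at discharge if earlier", measured by MoCA.
- Secondary outcome 4 is "cognitive function one month after surgery, used by the Revised Telephone Interview for Cognitive Status (TICS-m"), scored 0 to 50.
- Secondary outcome 3 is POCD. Section 4.2.5 repeats the definition: "POCD was defined as a 1 standard deviation decline in MoCA score on postoperative day 7, or at discharge if earlier, compared to baseline".

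Section 3.7.1 lists "Preoperative cognitive function status: used by Montreal Cognitive Assessment (MoCA") among the preoperative measures, and section 3.6.1 adds a MoCA on the day of surgery.

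Baseline cognition enters the analysis text in three places: inside the POCD definition, as a subgroup and interaction variable for delirium (section 4.2.3), and in an analysis at the end of section 4.2.5. That last analysis is called post hoc and also takes in centre, age, operative technique and education. It names neither the outcome nor the model.

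**The concern.** Where section 4.2.5 wants a model for a secondary outcome, it names one: zero-inflated Poisson for delirium duration and delirium-positive days, ordinal logistic regression for severity. It names none for the MoCA or TICS-m scores, so the default two-group tests govern them. This is a choice the protocol has made, in a section that it titles Statistical Analysis Plan, and not a detail left open.

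When a score is measured again after a short interval, the baseline value usually explains part of the later variation. Leaving it out widens the confidence interval and leaves any chance baseline imbalance in the estimate. At stake is how well the trial can estimate an effect of training on the cognitive scores themselves. The delirium result is not at stake.

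**Working it through.** **The plan's own figure.** The protocol sizes the trial on delirium only, 35% against 17.5%, two-sided 0.05, 80% power. With unpooled variance:

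n = (1.960 + 0.842)² × (0.35 × 0.65 + 0.175 × 0.825) / 0.175² = 95.3, so 96 per group; 96 / 0.9 = 106.7, so 107 per group and 214 in total.

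The stated figures reproduce. The protocol gives no SD, effect size or correlation for any cognitive outcome.

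**Inputs for the check.**

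- n = 96 per arm (section 4.1, before the dropout allowance).
- Two-sided 0.05 (sections 4.1 and 4.2.3).
- Correlation r between baseline and day-7 MoCA: not in the protocol; assumed 0.3 to 0.7.
- Effect on day-7 MoCA: not in the protocol; assumed 0.3 SD.

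**Formulas.** For a difference d in SD units:

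- Unadjusted test on the score: power = Φ(d / √(2/96) − 1.960).
- ANCOVA on baseline: the variance is multiplied by 1 − r², so power = Φ(d / √(2(1 − r²)/96) − 1.960), and the equivalent sample size per arm is 96 / (1 − r²).
- Smallest difference detectable with 80% power: (1.960 + 0.842) × √(2(1 − r²)/96).

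**Unadjusted result.** √(2/96) = 0.1443 and 0.3 / 0.1443 = 2.078, so power is Φ(0.118) = 55%. The difference detectable with 80% power is 0.404 SD.

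| Assumed r | Variance factor 1 − r² | Variance saved | Equivalent n per arm | Power at 0.3 SD | Detectable at 80% power |
|---|---|---|---|---|---|
| none (unadjusted) | 1.00 | – | 96 | 55% | 0.404 SD |
| 0.3 | 0.91 | 9% | 105 | 59% | 0.386 SD |
| 0.5 | 0.75 | 25% | 128 | 67% | 0.350 SD |
| 0.7 | 0.51 | 49% | 188 | 83% | 0.289 SD |

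**If the t test were applied to change from baseline.** The variance factor is 2(1 − r): 1.4, 1.0 and 0.6 at r = 0.3, 0.5 and 0.7. Power at 0.3 SD is then 42%, 55% and 77% (for r = 0.7: 0.3 / √(2 × 0.6/96) = 2.683, and Φ(0.723) = 0.765). ANCOVA is ahead at each of these values.

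**POCD.** A simulation of 1,500 trials per setting used 96 per arm, a 0.4 SD effect, a mean decline of 0.5 SD in routine care and a cut at 1 baseline SD, all assumed.

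| Assumed r | POCD, chi-square | POCD, logistic with baseline | Day-7 score, ANCOVA |
|---|---|---|---|
| 0.5 | 50% | 57% | 88% |
| 0.7 | 68% | 72% | 97% |

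Adjusting POCD for baseline adds 4 to 7 points. Most of the gap to the continuous analysis comes from dichotomising.

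**The case against.** The strongest case against is that nothing here is wrong. Allocation is 1:1 and stratified by site, so unadjusted t and rank tests are valid and unbiased. The outcomes are a few among 13 secondary ones, and the size of the loss rests on a correlation that the protocol does not give. At r = 0.3 the gain is 4 points of power. The general analysis paragraph also does not say whether raw or change scores are compared; at r = 0.7 a change-score t test would already recover most of the gain. All of this stands, and it limits the point to efficiency.

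A reader might also infer more than the documents support:

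- *That much of the precision is thrown away.* This follows only if r is at the upper end of the assumed range.
- *That POCD ignores baseline.* It is itself a decline from baseline MoCA, and adjusting it adds little. Secondary aim 2 names POCD, so it does not depend on unadjusted scores alone.
- *That baseline cognition is used nowhere else.* It is a subgroup variable for delirium and appears in the post-hoc analysis. That analysis does not close the gap, because it is tied to no outcome or model. It does show that the sponsor regards these covariates as relevant.
- *That the MoCA figures carry over to TICS-m.* TICS-m is a different instrument, given by telephone at one month, with no baseline TICS-m listed.
- *That all three MoCA time points lose precision.* One of them is baseline itself, where adjustment has no meaning.

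**Conclusion.** The point holds as a specific and inexpensive gain in precision for three secondary scores: preoperative MoCA, day-7 or discharge MoCA, and one-month TICS-m. The protocol fixes unadjusted tests for them and does not prespecify use of the baseline MoCA that it collects.

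For day-7 MoCA, reading the unadjusted test as one on the score itself, the variance saved is 9% to 49% over r = 0.3 to 0.7. The 0.3 SD effect is likewise assumed, and the formulas use a normal approximation. The same variance formula applies to preoperative MoCA with its own correlation, which is also not given. For TICS-m no figure can be stated. There is no bias or error-rate problem, and the primary analysis and the 214 patients are untouched.

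**What to change.** In section 4.2.5:

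1. Prespecify ANCOVA, or a mixed model covering both times, for preoperative and day-7 or discharge MoCA, with baseline MoCA, site, age and education as covariates. The MoCA covariate should be the baseline score, not the day-of-surgery score, which follows training and is itself one of the outcomes.
2. Prespecify ANCOVA for one-month TICS-m with the same covariates.
3. Report mean differences with 95% confidence intervals.
4. Keep POCD as defined, and present it alongside the continuous day-7 MoCA contrast.

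The cost is wording only. Site, age, education and baseline MoCA are already recorded, and no extra patients or visits are needed.
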